## Abstract

**Background:**

The effectiveness of bracing patients with IS has not yet been convincingly established due to a lack of RCTs. Some authors suggest that their results confirm that bracing is effective; others conclude that the effectiveness of bracing is doubtful or recommend a RCT. The aim of this study was to establish whether bracing patients with idiopathic scoliosis (IS) in an early stage will result in at least 5 degrees less mean progression of the curvature compared to the control group after two years of follow-up.

**Methods:**

A randomized controlled trial was designed. Eligible patients are girls and boys in the age group 8–15 years whose diagnosis of IS has been established by an orthopedic surgeon, who have not yet been treated by bracing or surgery, and for whom further growth of physical height is still expected based on medical examination and maturation characteristics (Risser ≤ 2). The Cobb angle of the eligible patient should either be minimally 22 and maximally 29 degrees with established progression of more than 5 degrees, or should be minimally 30 and maximally 35 degrees; established progression for the latter is not necessary. A total of 100 patients will be included in this trial. The intervention group will be treated with full-time Boston brace wear; the control group will not be braced. Every four months, each patient will have a physical and an X-ray examination. The main outcomes will be the Cobb angle two years after inclusion and health-related quality of life.

**Discussion:**

The results of this trial will be of great importance for the discussion on early treatment for scoliosis. Furthermore, the result will also be important for screening for scoliosis policies.

**Trial registration:**

Nederlands Trialregister ISRCTN36964733

## Background

Idiopathic scoliosis (IS) is defined as a lateral curvature of the spine of unknown origin with a minimal Cobb angle of 10 degrees. The Cobb angle is the angle between the upper most inclined vertebra and the lower most inclined vertebra. Besides a lateral curvature of the spine, there is a fixed rotation of one or more vertebrae and a rotational deformation of that vertebra. Once the curvature shows progression and exceeds a Cobb angle of about 20 to 25 degrees, the curvature is not likely to disappear spontaneously. Progression of the curvature usually occurs just before or during the growth spurt [1].

IS patients who are not fully grown and who have Cobb angles over 20–25 degrees with established progression of at least 5 degrees are usually treated with a brace [1]. A brace is a close fitting device applied to the trunk to try and prevent further progression of the curvature and thereby ultimately the need for surgical treatment. Surgical treatment may become necessary when not fully grown patients reach Cobb angles over 45–50 degrees [1].

Although many orthopedic surgeons feel that bracing might slow down progression of IS and some believe that reduction of the lateral curvature is also feasible, the effectiveness of early treatment of IS with a brace has not yet been established. No randomized controlled trial (RCT) on bracing for IS can be found in the Cochrane library or in PubMed. The majority of the studies are retrospective cohort studies. Some authors suggest that their results confirm that the brace is effective [2-4]; others conclude that the effectiveness of bracing is doubtful or recommend a RCT [5-8]. Some studies were performed without a control group; these study results are compared with results on the natural history from other studies. Another problem in the interpretation of the results of these studies is that they lack consistency regarding both inclusion criteria and the definitions of brace effectiveness [9]. In practice, there is currently no trial evidence that bracing IS patients is better than observation and watchful waiting [10-12]. Several Dutch orthopedic surgeons have reached consensus that a RCT is justified under the condition that the patients included are in an early stage of the clinical course of scoliosis [5]. In collaboration with these orthopedic surgeons, we formulated the current study design.

At first, serious doubts about this RCT were expressed, particularly regarding the willingness of IS patients to go through the process of randomization. In a preliminary study on the feasibility of a RCT on brace treatment for IS, we investigated the willingness of IS patients to accept the process of randomization. We tested the hypothesis that over 50% of IS patients with an early stage of IS visiting an orthopedic outpatient clinic, but not yet treated with a brace for this disorder, would be willing to participate in a RCT. The opinion of their parents was also explored. Parents of 30 patients were invited to participate in this pilot study, of which 21 (70%) agreed to do so. Patients and their parents were interviewed after receiving written information about the principle of randomization and the advantages and disadvantages of participating in a RCT on the effectiveness of brace treatment. This information was also verbally clarified at the beginning of the interview. In total, 87% of the patients (95%CI: 57% – 91%) and 70% of the parents (95%CI: 48% – 85%) agreed to participate in a RCT on bracing [13]. Table 1 shows the odds ratio for willingness to participate for some patient and parent characteristics. Fathers with a higher secondary education were borderline significantly more willing to participate in a RCT.

**Table 1 T1:** Odds ratios (OR) and 95% Confidence Intervals (C.I.) for willingness of parents to let their child participate in a RCT for treatment with bracing

Variables		Willingness of parents to agree with participation		OR (95% C.I.)
		Yes	No	
Age	per 1 year rise in age, in the range 9 to 15 years			1.28 (0.76–2.16)
Gender	boy girl	6 8	2 5	1.88 (0.27–13.12)
Native country father	Netherlands Other countries	12 2	3 4	8.00 (0.96–66.44)
Native country mother	Netherlands Other countries	13 1	4 3	9.75 (0.78–121.96)
Educational level father	=> higher secondary education < higher secondary education	9 5	1 6	10.75 (0.99–116.6)
Educational level mother	=> higher secondary education < higher secondary education	7 7	1 6	5.99 (0.56–63.53)

## Methods

### Setting

Orthopedic surgeons of 10 Dutch hospitals (3 teaching and 7 non-teaching hospitals) are willing to participate in this trial. Orthopedic surgeons will verbally inform all new patients who meet the inclusion criteria about the trial and give them written information (see table 2). Patients and their parents are asked for an informed consent. Together these orthopedic surgeons are expected to recruit 100 patients in a one-year period. All participating orthopedic surgeons have extensive experience with brace treatment in patients with IS.

**Table 2 T2:** Schematic overview of written information for (parents of) patients with idiopathic scoliosis

**Subject**	**Short explanation**
Background	- explanation what idiopathic scoliosis is - treatment options in early stages: brace or observation - effectiveness of brace treatment not established yet
Purpose	- establish whether early treatment with a brace prevents curve progression - evaluate the influence of treatment (brace vs. observation) on health-related quality of life
Design	- randomly assigned to brace or observation group by computer, no influence of patient, parent, orthopedic surgeon or researcher. 50–50% chance - all patients examined every four months, both groups same protocol - 4 times asked to fill in some questionnaires
Advantages and disadvantages	- not known yet who will have most advantages. brace group: maybe treated with effective brace; control group: delayed/no uncomfortable treatment of which effect has not been established
Risks	- both patients treated with a brace as patients being observed have risk on surgery; not yet known whether the risk is different between the groups - regular check-up; in case of progression > 10 degrees in patient in control group, the patient is available for brace
Closure	- end results after two years - depending on the results, again asked to give permission for follow-up until maturity
Voluntary participation	- participation is voluntarily, in case of refusal, the usual treatment in that hospital will be provided - can withdraw permission at any time of the study
Costs and incentive	- no extra costs for patients - no extra incentive for orthopedic surgeons for participation of a certain patient
Confidentiality	- all data will be treated confidentially - no names or data that can lead to identification will be used in rapports etc. - protocol was approved by medical ethical review board
Insurance	- Since no other treatment than currently used in the Netherlands is applied, an extra insurance for patients' safety was not necessary
Further information	- contact information of the researcher and an independent physician was supplied
Complaints	- contact information of a committee that handles complaints about the study

### Participants

Eligible patients are girls and boys in the age group 8–15 years whose diagnosis of IS has been established by an orthopedic surgeon, who have not yet been treated by bracing or surgery, and for whom further growth of physical height is still expected based on medical examination and maturation characteristics (Risser sign) established by X-ray. To expect further growth of physical height, only patients with a Risser sign ≤ 2 will be included. All participating orthopedic surgeons agreed that the Cobb angle of the eligible patient should either be minimally 22 and maximally 29 degrees with established progression of more than 5 degrees, or should be minimally 30 and maximally 35 degrees; established progression for the latter is not necessary. At inclusion of the study, data on calendar age, gender, height, maturation characteristics (Risser sign, menarche), size and location of the curvature will be recorded for all patients.

### Ethical Committee Approval

The Medical Ethical Review Board of the coordinating hospital approved this trial in December 2005 (MEC-2005-319). All other participating centers (n = 10) obtained approval from their local Medical Ethical Committee between March 2006 and June 2007.

### Intervention group

Early treatment of IS consists of wearing a brace that is intended to prevent the curvature from worsening. Patients in the intervention group will initially be braced for two years. The orthopedic surgeon will refer the patients to a qualified certified prosthetist orthotist who will measure, make and fit the brace. Each brace will be measured and modified individually for each patient to fit and correct her/his curvature. She/he will be advised to wear the brace every day for 18–23 hours. Boston braces will be used for all patients; this brace is used the most in the Netherlands. Patients are usually advised to attend physical therapy for muscle training and to correct body posture. Physical therapy alone is not expected to prevent further progression of the curvature [11]. Therefore, patients are free to choose whether or not they will attend physical therapy.

Although some orthopedic surgeons prefer to keep the patients in the hospital for a few days to allow them to become used to wearing the brace, others do not. The orthopedic surgeons are allowed to apply their own protocol concerning this hospital admission.

In case patients of the intervention group reach Cobb angles that require surgery, they can be operated.

### Control group

Patients in the control group will initially not be braced during the two study years, unless their curvature shows more than 10 degrees progression compared to the Cobb angle at inclusion. In this case, the orthopedic surgeon, patients and their parents could decide to start brace treatment. The patients in the control group are allowed to attend physical therapy if they want to, because physical therapy alone will not prevent further progression of the curvature.

In case patients of the control group reach Cobb angles that require surgery, they can be operated.

### Follow-up

Both the intervention and control group will follow the same protocol for monitoring the curvature during the two years of the study. Every four months the orthopedic surgeons will repeat the measurements of size and location of the abnormal curvature, physical height, maturation characteristics (menarche and Risser sign), brace compliance, and whether or not surgery is indicated. These examinations will be conducted following a specific protocol: every four months a physical examination and an X-ray of the spine will take place. Patients will take off the brace the night before an X-ray is taken. Standard technique is a standing position of the patient and a posteroanterior projection. In patients with discrepancy in leg length, boards will be put under the shortest leg to correct for this.

### Objectives

The purpose of this RCT is to establish whether brace treatment in IS patients with Cobb angles between 22 and 35 degrees significantly reduces further bending of the spine, thereby preventing surgery for some patients. The specific research questions are:

1. Will bracing patients with IS in an early stage result in at least 5 degrees less mean progression of the curvature compared to the control group after two years of follow-up?

2. Do differences in health-related quality of life exist between patients with IS who are treated with a brace and patients who are under watchful waiting?

3. If bracing proves to be effective, what is the cost-effectiveness of brace treatment, compared to regular surveillance only in terms of cost per avoided surgery and cost per QALY, accounting for the (increased) burden of bracing and the (reduced) burden of surgery? If bracing does not appear to be effective, what are the possible savings if treatment guidelines would be changed?

4. If bracing proves to be effective, what is the cost-effectiveness of the nationwide screening program for scoliosis?

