### Outcomes

The primary outcome of this RCT is that bracing will be considered potentially effective, if after two years the mean progression of the abnormal curvature in the intervention group is at least 5 degrees less than in the control group. Two years after date of randomization the primary outcome measure, progression in Cobb angle, will be established in each patient. Mean Cobb angles, as reported independently, in the intervention arm will be compared to mean Cobb angles in the control arm. To reduce inter-observer measurement errors, two orthopedic surgeons associated with the project team will judge all X-rays independently and without knowledge of the allocation arm. The mean value of the observed Cobb angles will serve as assessed value, whenever the difference between the two measurements is less than 3 degrees. If the difference is larger, a third orthopedic surgeon will be asked to measure the Cobb angle; the mean Cobb angle of all 3 measurements will serve as the assessed value.

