### Sample size

The Cobb angle at inclusion will on average be 29 degrees (range 22–35 degrees). Due to the standard error of radiographic production and intra and inter-observer measurement variation, a measurement error in Cobb angles of 5 degrees will appear [1]. To reduce the standard error of radiographic production, all patients will undergo X-ray following a strict protocol. Because inter-observer measurements errors are reduced (see *Outcomes*), measurement error will than be maximal 2 degrees, thus the 95% observation interval of Cobb angles at inclusion is 20–37 degrees. After two years, when the outcome will be determined, the range in change will be 0–15 ± 2 degrees. Assuming a uniform distribution of this change in Cobb angle between the patients after two years (most unfavorable scenario), the standard deviation of the difference in change between baseline and outcome measurement will be about 4.5 degrees.

Since bracing has to be better than observation to be justified as treatment for IS, a superiority design will be used. With a power of 95% and alpha = 0.05, a mean difference of 5 degrees between the groups can be detected with 40 patients in both study arms. We will aim at a study population at start of 100 patients to take loss to follow-up into account.

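### Question 3 estimates cost-effectiveness only after a verdict that bracing works, and otherwise asks only for savings, so a real effect that misses the verdict may be left out of the economic result

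*Protocol article*

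**What the plan says.** The Objectives section of the protocol article gives question 3 two branches.

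- **Positive verdict:** "If bracing proves to be effective, what is the cost-effectiveness of brace treatment, compared to regular surveillance only", expressed as cost per avoided surgery and cost per QALY.
- **Negative verdict:** "If bracing does not appear to be effective, what are the possible savings if treatment guidelines would be changed". No QALY, surgery or other health term appears here.

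Question 4 carries the same condition: "If bracing proves to be effective, what is the cost-effectiveness of the nationwide screening program for scoliosis".

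Question 3 does not define the verdict. The article offers more than one standard:

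- **Outcomes:** "bracing will be considered potentially effective, if after two years the mean progression of the abnormal curvature" beats the control arm by a margin of 5 degrees or more. Question 1 and the abstract use the same 5-degree line.
- **Objectives, purpose statement:** bracing is to be tested for whether it "significantly reduces further bending of the spine, thereby preventing surgery for some patients", with no threshold in that sentence.
- **Sample size:** "Since bracing has to be better than observation to be justified as treatment for IS, a superiority design will be used".

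Other parts of the plan carry no such condition. Question 2 and Statistical methods compare quality of life and utilities between the arms whatever the primary result. EuroQol is collected in both arms (Outcomes), and whether surgery is indicated is recorded every four months in both arms (Follow-up).

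**The concern.** Cost per QALY and cost per avoided surgery are estimates with uncertainty. They do not need a positive primary result to be meaningful, and a decision about guidelines needs them most when the effect is modest. As worded, a trial that misses its effectiveness standard produces a savings figure with no health change next to it.

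That figure could omit health lost by withdrawing a modestly effective brace. It could equally omit quality of life gained by sparing children a treatment that the article itself calls burdensome. The article also expects dilution: the compliance paragraph in Outcomes says that poor brace wear would make the effect look smaller than it is. A real effect observed below the line is therefore a foreseeable result.

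There is a second consequence. If cost-effectiveness is calculated only after a favourable verdict, the effect that feeds it has been selected for being high.

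**Working it through.** **Inputs** (Sample size section): difference 5 degrees, SD of change about 4.5 degrees, 40 patients per arm, and "With a power of 95% and alpha = 0.05". Sidedness is not stated; two-sided is assumed below.

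**The plan's own figure.** n per arm = 2 × SD² × (1.96 + 1.645)² / 5² = 2 × 20.25 × 13.0 / 25 = 21.05, so 22 per arm (18 if one-sided), against 40 stated. The figure is not reproduced. The SD at which 40 per arm gives 95% power is 5 × √20 / (1.96 + 1.645) = 6.2. The mismatch is a separate matter and errs towards more power, but it means the size of this point must be shown for both SD 4.5 and SD 6.2.

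**Standard errors at 40 per arm.** SE = SD × √(2/40).

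- SD 4.5: SE = 1.006; smallest significant difference 1.96 × 1.006 = 1.97 degrees.
- SD 6.2: SE = 1.386; smallest significant difference 1.96 × 1.386 = 2.72 degrees.

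**If the condition is an observed difference of at least 5 degrees** (normal approximation). P(observed ≥ 5) = 1 − Φ((5 − δ)/SE), where δ is the true effect. P(significant and below 5) = P(significant) − P(observed ≥ 5).

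| True effect δ | SD | P(observed ≥ 5) | P(significant) | P(significant, below 5) |
|---|---|---|---|---|
| 3 | 4.5 | 2% | 85% | 82% |
| 4 | 4.5 | 16% | 98% | 82% |
| 5 | 4.5 | 50% | 99.9% | 50% |
| 3 | 6.2 | 7% | 58% | 51% |
| 4 | 6.2 | 24% | 82% | 59% |
| 5 | 6.2 | 50% | 95% | 45% |

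For δ = 4 and SD 4.5: (5 − 4)/1.006 = 0.994 and Φ(0.994) = 0.84, so 84% of trials fall below 5. Significance has probability 0.978, and 0.978 − 0.160 = 0.818.

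**If the condition is significance instead.** The share of trials that miss it despite a real effect is 1 − P(significant). For a true 3 degrees this is 15% at SD 4.5 and 42% at SD 6.2; for a true 4 degrees it is 2% and 18%. The problem shrinks but does not vanish.

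**Selection.** The mean observed effect among trials that pass the 5-degree line is δ + SE × φ(a)/(1 − Φ(a)), with a = (5 − δ)/SE. For δ = 4 this is 5.5 degrees at SD 4.5 and 5.8 at SD 6.2. A cost-effectiveness result reported only in those trials would rest on an effect overstated by about 1.5 to 1.8 degrees.

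**The case against.** **The 5-degree condition is inferred.** A reader might take question 3 to say that cost-effectiveness is calculated only if the 5-degree rule is met. It does not say so. The Outcomes section attaches 5 degrees to a weaker phrase (only potentially effective), and the purpose statement and Sample size section use significance and superiority. Under those standards a significant 3-degree effect would enter the cost-effectiveness branch. This stands. The 5-degree reading is the most natural one, given question 1, but the percentages for the 5-degree line depend on it and on treating it as a cut-off for the observed difference.

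**No rule sets a smaller effect to zero.** A reader might infer that the savings branch values such an effect at nothing. The article does not state this: that branch names no health term, but excludes none. The supportable statement is that the effect may be left out.

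**Quality of life is not hidden.** A reader might also infer that a negative verdict would conceal the burden or benefit of bracing. Statistical methods contradicts that, since utilities are compared without condition. The loss is confined to the incremental ratios.

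**A fuller economic plan may exist.** An article commonly leaves economic methods to other documents, so missing detail on bootstrapping or costing is no fault here. The conditional wording of question 3, however, is stated outright.

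**Conclusion.** The point holds in a limited form. Question 3 ties cost per QALY and cost per avoided surgery to an effectiveness verdict whose standard the article does not fix, and its negative branch names no health effect. Under either candidate standard, failing the test does not show absence of effect.

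On the 5-degree reading, with 40 per arm, two-sided alpha 0.05 and a normal approximation, a true effect of 4 degrees gives a significant result outside the cost-effectiveness branch in about 59% (SD 6.2) to 82% (SD 4.5) of trials. A true effect equal to the design value of 5 degrees misses in half of trials at either SD. On a significance reading the exposure is smaller, as shown above.

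The change should be made, but it concerns a downstream objective. Randomization, the primary endpoint, the sample size and the collection of utilities are unaffected.

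**What to change.** Reword question 3 so that the incremental costs, QALYs and avoided surgeries of bracing versus observation are estimated, with their uncertainty, whatever the primary result. Present any savings from a guideline change together with the estimated health change, not in place of it.

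The cost is a change of wording and a little more analysis work. Utilities and surgery indication are already collected in both arms. The article does not describe how costs are collected, but both existing branches of question 3 already require cost data, so the rewording does not create that need.
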